## Abstract

**Background:**

Although physical therapy and falls prevention education are argued to reduce falls and disability in people with idiopathic Parkinson's disease, this has not yet been confirmed with a large scale randomised controlled clinical trial. The study will investigate the effects on falls, mobility and quality of life of (i) movement strategy training combined with falls prevention education, (ii) progressive resistance strength training combined with falls prevention education, (iii) a generic life-skills social program (control group).

**Methods/Design:**

People with idiopathic Parkinson's disease who live at home will be recruited and randomly allocated to one of three groups. Each person shall receive therapy in an out-patient setting in groups of 3-4. Each group shall be scheduled to meet once per week for 2 hours for 8 consecutive weeks. All participants will also have a structured 2 hour home practice program for each week during the 8 week intervention phase. Assessments will occur before therapy, after the 8 week therapy program, and at 3 and 12 months after the intervention. A falls calendar will be kept by each participant for 12 months after outpatient therapy.

Consistent with the recommendations of the Prevention of Falls Network Europe group, three falls variables will be used as the primary outcome measures: the number of fallers, the number of multiple fallers and the falls rate. In addition to quantifying falls, we shall measure mobility, activity limitations and quality of life as secondary outcomes.

**Discussion:**

This study has the potential to determine whether outpatient movement strategy training combined with falls prevention education or progressive resistance strength training combined with falls prevention education are effective for reducing falls and improving mobility and life quality in people with Parkinson's disease who live at home.

**Trial registration:**

Australia and New Zealand Clinical Trials Register (ANZCTR): ACTRN12606000344594

## Background

Falls are common in people with idiopathic Parkinson's disease (PD) and fall related injuries can be associated with immobility and reduced quality of life. Many people with PD experience difficulties walking and balancing as the disease progresses and this can compromise their ability to participate in work, family, community and social activities [1,2]. Previous research suggests that more than half of people who are diagnosed with PD experience one or more falls in a given 12 month period, compared to 30% of older adults who live in the community [3-8]. The extent to which falls in people with PD are related to hypokinesia, dyskinesa, postural instability, rigidity, weakness, cognitive impairment or medication remains unclear. The associated burden of disease arising from falls and immobility can impact adversely on individuals, their families, the healthcare system and society.

At the present time there is no known cure for idiopathic PD. Pharmacological therapy currently provides the most effective symptomatic treatment for many movement disorders [9]. Nevertheless freezing of gait, postural instability and hypokinesia have only a limited or short-lived response to PD medication in many individuals [10]. As the disease progresses, PD medications are adjusted in response to changes in symptoms [11]. Despite the best medical management, motor fluctuations and movement disorders can recur due to progressive cell loss in the substantia nigra pars compacta in the brainstem and disruption to neural connections to the frontal lobes, cerebellum and other regions of the brain [12]. For these reasons, pharmacological management is often augmented by physical therapy and falls education [13].

There are two main approaches to physical rehabilitation for people with PD. Movement strategy training (MST) teaches individuals how to cope with their movement disorders by using attention, cues, environmental adaptation, part practice and mental rehearsal [14]. Rather than regulating well learned movements automatically through the defective basal ganglia circuitry, MST aims to train people to use the frontal cortex in the initiation and execution of movements and functional activities. Motor performance is optimised by breaking down complex movement sequences into small parts and by teaching people to focus their attention on each part prior to "whole" task practice [13]. Mental rehearsal of forthcoming movements, focussing on the movement while it is occurring and the use of visual or auditory cues to guide motor performance are additional strategies [13,15]. Other "tricks" include performing the movement in a different way (e.g., running or dance steps instead of walking) and using different intent (e.g., thinking about getting to the fridge to get the milk rather than thinking of trying to walk).

The other key approach to improving movement in people with PD is progressive resistance strength training (PST) [16-20]. People with PD can become weak and de-conditioned due to inactivity, disuse and reduced physical activity associated with hypokinesia and ageing [17,18]. There is preliminary evidence that PST might improve muscle strength [18,21,22] with associated improvements in balance [21] and walking [18,19] in some people. The extent to which PST prevents falls in people with PD remains unclear.

Education packages that provide advice about the predictors of falls and how to prevent them are also thought to be effective in reducing falls, either as a single intervention or as part of a multifaceted treatment package [23-26]. Although a range of approaches and methods of delivery have been used, these packages generally aim to increase awareness of a person's risk of, and risk factors for, falling, as well as to help them identify and access resources to undertake appropriate interventions.

The primary aim of the current study is to conduct the first large scale community based trial to investigate if outpatient physical therapy programs comprising either (i) MST combined with falls education or (ii) PST combined with falls education are more effective than a control group that receives a generic "life-skills" program that does not contain any information or advice about gait, balance, falls, exercise or mobility. We hypothesise that participation in physical therapy directed to either MST or PST combined with falls education will reduce falls relative to participation in the control group. Participation in an active therapy group is also predicted to provide significant improvements in mobility and quality of life, which are not expected to occur for the control group. The anticipated reduction in falls rate in the therapy groups is likely to be accompanied by cost benefits, as we have described in an earlier paper [27].

## Methods

### Design

A single blind, parallel-group randomised controlled clinical trial (RCT) design will be used with two intervention groups and one control group. Because the literature at the time of study design did not provide evidence on whether movement strategies were superior to strengthening, we included one group receiving MST and another receiving PST. To reflect clinical practice, each of these groups will also receive a falls prevention education program [28]. A control group that does not include physical therapy or falls education will be used to determine the relative effectiveness of each therapy approach. Ethical approval to conduct the study has been gained from the University of Melbourne Health Sciences Human Ethics Sub-Committee (0828579). Written consent for publication will be obtained from the participant or their relative.

### Participants

Community dwelling people with PD will be recruited for the trial from outpatient movement disorder clinics, community-based rehabilitation programs, PD support groups and private neurologists in the Melbourne metropolitan area. Participants will also be recruited from the local community through advertisements in local and metropolitan newspapers and newsletters distributed by Parkinson's Victoria, Australia. Potential participants will be provided with an information pack describing the study, and invited to return an 'expression of interest' to the study coordinator to be screened for eligibility. To be included, participants will be required to have confirmed idiopathic PD, be able to participate in an outpatient exercise program including strength training and be willing to complete a falls calendar for 12 months after therapy. Participants will be excluded if they score less than 24 on the Mini-Mental State Examination (MMSE) [29], or if they have a rating greater than 4 on the modified Hoehn and Yahr scale [30] or if they are on major tranquilizers.

### Sample size

The sample size for the study was determined based on the falls rates and effect sizes obtained from previous trials on people with PD and the elderly [6,31,32]. For each sample size calculation, power was set at 80%, alpha set at 5%, and the drop-out rate was set at 15%. For falls, a sample size of 110 was thought to be required to detect a 20% difference between the groups, assuming a falling rate of 60% in the control group. For walking speed, a sample size of 74 was required to detect a 10% difference between the groups, assuming a mean (± SD) walking speed in the control group of 58.4 (12.0) m/min. For the "timed up and go" test, a sample size of 83 was thought to be required to detect a 10% difference between the groups, assuming a mean (± SD) timed up and go in the control group of 13.78 (2.99) sec. Thus, to ensure adequate statistical power for each of these outcome measures, the sample size for the study would optimally be 110 per group (total n = 330). Approximately 60 percent of control group participants are expected to fall between Test 1 (baseline) and Test 4 (12 months after therapy) with falls reduced to around 40% in the two active therapy groups.

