### Outcome measures

All participants will be tested by trained blinded assessors before and after the 8 week interventions, and at 3 months and 12 months after completion of the intervention phase. Participants will keep a falls calendar for 12 months after therapy. Consistent with the recommendations of the Prevention of Falls Network Europe (PrOFaNE) group, a fall will be defined as "an unexpected event in which the participant comes to rest on the ground, floor, or lower level" [35]. Each time a participant falls, they will tick the date on the falls calendar and then telephone a falls hotline where they will be interviewed about the nature of the fall, circumstances, injuries sustained, healthcare required and other factors. The falls interview questions are given in Figure 1, and an example of a calendar page is provided as an additional file (see Additional File 1).

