**Figure 1 F1:**
[figure not shown]
**Falls interview questions**.

The three falls outcomes that are the primary outcomes are (i) the number of fallers in each group (ii) the number of multiple fallers in each group and (iii) the falls rate over 12 months in each group. Secondary outcome measures will include the number of injurious falls, defined as a fall requiring a visit to a health service provider. Additional secondary outcome measures include mobility, measured by quantifying walking speed using the 6m walking test and the Timed Up and Go Test [36]. Activity limitations will be quantified using the United Parkinson's Disease Rating Scale sections II and III [37]. Quality of life will be measured using the Parkinson's Disease Questionnaire-39 (PDQ39) [38] and EuroQol-5D [39]. Changes in health-related QoL will be measured using both a PD-specific measure (PDQ-39) and a generic utility instrument (Euroqol-5D) administered at baseline, immediately post-intervention, 3 months, and 12 months. Safety during the intervention phase will be assessed by time to first fall, and monitoring of adverse events related to therapy.

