### Statistical analysis

Statistical analysis will be undertaken using IBM SPSS version 19.0 (SPSS Corp, Chicago, Ill, USA) and STATA 8 (Stata Corp, College Station, Tex., USA) statistical software. All analyses will be conducted on an intention-to-treat principle using all randomised participants. Demographic characteristics and baseline data will be summarised by descriptive statistics. For the primary outcome measures, the number of fallers and multiple fallers in each group will be compared by calculating relative risks. The number of falls and falls rate per person per year in the three groups will then be compared using negative binomial regression models. This approach takes into account all falls and adjusts for varying duration of follow-up [40,41]. As a safety measure, time to first fall during the intervention period will be analysed using Kaplan-Meier survival analysis, and comparisons between groups will be made using the Mantel-Cox log rank test. The continuously-scored secondary outcome measures at baseline and the follow-up appointments will be compared using analysis of covariance with baseline scores and intervention group entered as independent variables [42,43]. For categorical secondary outcome measures, relative risks will be used to analyse differences between the groups.

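### The faller risks behind the sample size run from baseline to 12 months after therapy, but the falls calendar behind the primary outcomes starts only after therapy

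*Protocol article*

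**What the plan says.** **Planning assumption.** The Sample size section of the protocol article sets the design values: "power was set at 80%, alpha set at 5%, and the drop-out rate was set at 15" per cent. It then derives the number per group from the proportion of fallers: "a sample size of 110 was thought to be required to detect a 20% difference between the groups, assuming a falling rate of 60" per cent in the control group. That sentence names no time window. The window comes at the end of the same section: "Approximately 60 percent of control group participants are expected to fall between Test 1 (baseline) and Test 4 (12 months after therapy"), with about 40% in each active group.

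**Observation.** The Outcome measures section says: "Participants will keep a falls calendar for 12 months after therapy". The abstract gives the same period, and the eligibility criteria under Participants ask for willingness to keep the calendar over it. Of the three primary outcomes, only the third has a stated period: "iii) the falls rate over 12 months in each group". Fallers and multiple fallers have none.

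**Falls during therapy.** The Outcome measures and Statistical analysis sections treat time to first fall in the intervention phase as a safety measure, analysed by Kaplan-Meier and log rank. The only recording tools described are the calendar and the telephone hotline linked to it, and the calendar is placed after therapy.

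**Analysis set.** The Statistical analysis section says: "All analyses will be conducted on an intention-to-treat principle using all randomised participants". The falls rate is to be modelled by negative binomial regression, which allows for unequal follow-up.

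**The concern.** A proportion of fallers has meaning only with its window, because more people have fallen at least once after 60 weeks than after 52. The article plans on one window and describes data collection for another. A reader cannot tell whether someone who falls only in week 4 of therapy counts as a faller in the primary analysis.

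Two things are at stake.

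- **Power.** The risks that justify 110 per group may be higher, and further apart, than those the calendar can show.
- **Analysis set.** With a window that opens 8 weeks into the study, a participant who leaves the study during therapy contributes nothing to the primary outcomes. The arms offer different programmes (exercise or movement training v a social programme), so such losses could differ between them. A drop-out allowance protects the numbers. It does not protect the comparison against selective loss.

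**Working it through.** **Inputs.** From Sample size: 60% v 40%, 80% power, 5% alpha, 15% drop-out, 110 per group. From the intervention description: 8 weeks of therapy. Test 1 to Test 4 is then 8 + 52 = 60 weeks, and the calendar covers 52. Assumed here, because not stated: two-sided alpha and pairwise comparison with control.

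**Step 1: the plan's own figure.** With unpooled variance, n = (1.96 + 0.8416)² × (0.6×0.4 + 0.4×0.6) / 0.20² = 7.849 × 0.48 / 0.04 = 94.2, so 95 evaluable per group. Adding 15% gives 95 × 1.15 = 109.25, rounded up to 110. Dividing by 0.85 gives 112. The stated 110 reproduces.

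**Step 2: reference power.** Evaluable per group: 110 × 0.85 = 93.5. The pooled-variance formula is

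power = Φ{[d√n − 1.96√(2p̄q̄)] / √(p₁q₁ + p₂q₂)}.

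For 60% v 40%: (0.20 × 9.670 − 1.96 × 0.7071) / 0.6928 = 0.791, so power is 78.6%. The shortfall from 80% at this step comes mainly from the choice of formula and has nothing to do with the window.

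**Step 3: move the risks to 52 weeks with a constant hazard.**

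- Control: 1 − 0.4^(52/60) = 54.8%.
- Active: 1 − 0.6^(52/60) = 35.8%.
- Difference: 19.0 points.
- Power: (0.1903 × 9.670 − 1.96 × 0.7040) / 0.6910 = 0.666, so 74.7%.

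Using 12/14 months instead of 52/60 weeks gives 54.4% v 35.5% and 74.4%. The window costs about 4 points (78.6% to 74.7%). For 80% power at these risks, 107 evaluable per group would be needed, or 107 / 0.85 = 126 enrolled.

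**Step 4: other assumptions, all with 93.5 per group.** For gamma frailty with variance θ, survival is (1 + θH)^(−1/θ). H is solved from 60% and 40% at 60 weeks, then multiplied by 52/60. For no effect during therapy, the active arm carries the control hazard for 8 weeks: its cumulative hazard of 0.511 less 0.916 × 8/60 = 0.122 leaves 0.389, a risk of 32.2%.

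| Assumption for the 12-month window | Control v active | Power |
|---|---|---|
| Constant hazard | 54.8% v 35.8% | 74.7% |
| Frailty, θ = 0.5 | 55.8% v 36.2% | 76.9% |
| Frailty, θ = 1 | 56.5% v 36.6% | 78.3% |
| Frailty, θ = 2 | 57.6% v 37.3% | 79.8% |
| 20-point difference kept | 55% v 35% | 79.0% |
| No effect during therapy | 54.8% v 32.2% | 88.3% |
| 60%/40% already 12-month risks | 60% v 40% | 78.6% |

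**Step 5: the analysis set.** A participant lost before the calendar starts has zero exposure. In a rate model the offset is the log of exposure, so that person cannot enter. In the relative risk for fallers, the person is either left out or counted as a non-faller without having been observed.

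**The case against.** Three stronger readings are tempting, and the article does not support them.

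- **That falls are recorded only after therapy.** The planned time-to-first-fall analysis means that falls during therapy are meant to be captured. Only the calendar is confined to the later period. How the earlier falls are recorded is a detail that an article may leave to the full protocol. What remains is that these falls are assigned to safety, while the sample-size text counts the same weeks in the primary risk.
- **That the stated 80% power is not delivered.** The 110 reproduces. The loss of about 4 points needs a constant hazard, which the article does not state, and even the direction of the change depends on the assumption. The full 15% drop-out is already removed in these figures; with all 110 evaluable, the constant-hazard risks give 81.4%. The sentence that derives 110 names no window, and the Background reports that more than half of people with Parkinson's disease fall in a 12-month period. The 60% may therefore be a 12-month figure with a loose label.
- **That early drop-outs cannot enter the intention-to-treat analysis.** People who stop therapy but stay in the study can keep the calendar, and those lost later enter the rate model with shorter follow-up. The problem is confined to people who leave the study before the calendar starts.

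It is also fair to say that counting falls only after a completed programme, with falls during the programme analysed as safety, is a coherent design, and that rules for missing data may sit in the analysis plan. Neither point removes the conflict, because the article's own planning text uses the other window and its analysis text claims everyone randomised.

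**Conclusion.** The point holds as an unreconciled mismatch. The sample-size risks are stated for about 60 weeks from baseline, while the primary falls data come from a calendar covering the 12 months after therapy.

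The consequence for power is conditional. If 60%/40% belong to the longer window, 80% is not supported for the calendar window in most of the cases tried: 74-75% under a constant hazard and 77-80% under frailty or an unchanged 20-point difference. If treatment does nothing during therapy, power is higher, at about 88%. If 60% is a 12-month figure, power is unaffected and only the label needs correcting. The article does not allow a choice among these, so a reader should not conclude that the trial is underpowered.

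The consequence for the analysis set does not depend on those assumptions. With a post-therapy window, participants lost to the study before the calendar starts have no observed primary falls data, so the all-randomised statement cannot hold for the falls outcomes. How many people this affects cannot be told from the article.

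**What to change.** **Preferred.** Issue the existing calendar at Test 1. Define one window for fallers, multiple fallers and falls rate, and state the 60%/40% risks for that same window. One example is randomisation to Test 4, with observed person-time as the exposure in the rate model and the 12 months after therapy as a prespecified supportive analysis. The article does not say whether Test 1 and randomisation coincide, so the starting point should be named. This also gives the safety analysis of falls during therapy a data source. The cost is 8 more weeks of calendar keeping per participant and an amended sentence or two in Sample size, Outcome measures and Statistical analysis.

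**Alternative.** Keep the post-therapy window, say so for all three primary outcomes, and restate the assumed 12-month risks and the power with its range. If the 60% is already a 12-month figure, saying so is enough on this point. Qualify the all-randomised statement for the falls outcomes, and say how participants lost before the calendar starts are handled. The cost is a stated power that may be slightly less favourable.

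Neither option needs extra patients. The choice should be made before outcome data are seen by group.

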### Interventions

#### Movement strategy training (MST)

All interventions will be delivered by therapists trained in the standard protocols. The MST group will attend two hours of physical therapy weekly in an outpatient setting for eight sequential weeks, in small classes of three or four participants. The MST group will follow a program based upon the principles of physical rehabilitation outlined in Morris et al., [13,33,34]. Table 1 summarises the content and dosage of the MST program with guidelines for therapists. Movement strategies emphasise task specific practice of everyday functional actions such as rolling over, standing up, walking, crossing obstacles and turning. These tasks are practised with strategies such as visual or auditory cues, mental rehearsal and movement planning, conscious attention during the task, and breaking the task into a sequence of smaller components. The program is tailored to movement impairments, activity limitations, and cognitive status and learning ability. An individualised home practice session of strategies to practise within the home or community will also be completed once a week. Structured falls risk education will also be provided each week, based upon the content of a booklet *Don't fall for it. Falls can be prevented! - A guide to preventing falls for older people *produced by the Australian Commonwealth Department of Health and Ageing [28]. This booklet contains information on topics such as medication, vision, footwear, regular activity and safe environments. A single home visit will be conducted by a trained therapist or nurse to check compliance with the therapy program.

**Table 1 T1:** Movement strategy training protocol

**Principles of Movement Strategy Training **[13,33,34,44]

• Use visual, auditory or somatosensory cues to optimise timing and amplitude of actions, movements and their components
• Use attentional strategies such as focussing on key movement components, visualising correct amplitude or pattern, mental rehearsal, visualisation
• Break down complex movements into parts and focus on each segment in sequence
• Practise individual components of activities separately before incorporating into whole
• Incorporate cues and attentional strategies into functional tasks with reference to home environment.
• Individualise strategies, repetitions, and environmental context, with consideration to level of disability and functional difficulties
• For people with mild levels of impairment, consider practising dual tasking to promote motor learning. For those with advanced disease, avoid dual tasks

